### Reporting of data and statistical analysis

#### Descriptive statistics

Descriptive statistics for categorical variables will be presented using frequency tables, and continuous variables will be presented as each mean and s.d.^
47
^ The incidence of biological and technical complications will be reported.^
47
^

#### Single/multiple analysis

Our hypotheses will be tested using multilevel regression analyses.^
32
^ As for the main aim of the study, hypotheses about associations between SB and the occurrence of technical complications or loss of osseointegration will be tested by using a Cox proportional hazards regression model.^
48
^ Possible associations between SB and bleeding on probing, pocket depths and marginal bone height will be tested by means of linear regression analysis. Likewise, for our secondary aim, possible associations between SB and microbiome diversity will be tested by means of linear regression analysis. The regression models will be expanded to examine the effects of confounders and covariates on the associations between main predictor and main outcomes. We aim to adjust our analysis for dependency of data, which arises from the fact that multiple implants can be placed in one subject, thus violating the assumption of independent observations.^49
^

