### Objective of the present study

To contribute to the understanding of the time-dependent associations between SB and complications of dental implant treatments, we aim to perform a prospective cohort study. Our main aim is to answer the research question: ‘Is sleep bruxism a risk factor for (peri-)implant complications?’. SB will be monitored by measuring masticatory muscle activity during sleep. The investigation will have two main outcomes, namely, technical complications and biological complications. As to avoid variation in the outcomes caused by failing retention of removable suprastructures, we will confine our study population to patients treated with fixed suprastructures.

The following null hypotheses are formulated: (1) Sleep bruxism is not associated with the occurrence of technical complications. Outcomes of interest are: suprastructure complications, abutment complications, implant fractures or other technical failures (see ‘Variables’ paragraph for a more comprehensive description of all variables), and (2) SB is not associated with the occurrence of biological complications. Main outcomes related to this hypothesis are: differences in marginal bone height, peri-implant bleeding on probing, pocket depths and loss of osseointegration.

Our secondary aim is to examine whether there is an association between SB activity and the composition of peri-implant submucosal biofilm. For this purpose, the null hypothesis is: SB is not associated with species diversity of peri-implant submucosal biofilm. The main outcome will be peri-implant submucosal microbiome diversity.

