#### Outcomes

##### Biological complications

Biological complications will be assessed by examining cardinal features of peri-implant health, i.e., bleeding on probing, probing depths and marginal bone height.^37
^ Also, loss of osseointegration will be registered.

Peri-implant bleeding on probing will be scored per implant according to the Modified Gingival Index^
38
^ as follows:

- Score 0; no bleeding when a periodontal probe is passed along the gingival margin adjacent the implant;- Score 1; isolated bleeding spots visible;- Score 2; blood forms a confluent red line on margin;- Score 3; heavy or profuse bleeding.

Peri-implant probing depths will be scored using a standardised periodontal probe (Click-Probe 3/5/7/10 blue, KerrHave, Bioggio, Switzerland) with pressure of 0.2–0.25 N. Clinical probing depth will be measured in millimetre as the distance from the mucosal margin to the bottom of the deepest clinical probing site on each side of the examined implant (mesial, distal, buccal and lingual). Per implant, the mean value of those sides is calculated.

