Marginal bone height will be assessed radiographically. Vertical bitewing radiographs will be taken using the parallel cone technique and phosphor plates (VistaScan Image Plate, Dürr Dental, Bietigheim-Bissingen, Germany), with the assistance of individually modified plate positioning devices. Modification of the positioning devices will aim at acquiring geometric reproducibility of the radiographs during the successive examinations of the participants. More specifically, reproducing the intraoral position of the device will be achieved by using a silicone (Provil Novo, Putty regular set, Heraeus Kulzer, Hanau, Germany) mould, made just after the suprastructure is placed. A reproducible position of the X-ray tube with respect to the plate positioning device will be acquired by the use of a customised hard plastic aiming block. Radiographs are taken with a dental X-ray generator operated at 63 kV DC, 8 mA, and exposure time of 0.32 s. The obtained images will be imported in a commercial dental image archiving program (Emago, Oral Diagnostic Systems, Amsterdam, The Netherlands). Marginal bone height will be measured on each radiograph using the appropriate tool of the program as the vertical distance (mm) from a fixed landmark point on an implant (implant shoulder) to the superior border of the marginal bone at each of the mesial and distal sides of the implant. The Subtraction technique of the Emago software will be used to detect differences in marginal bone between subsequent radiographs. Measurements will be performed by two independent examiners. Per implant, the mean value of both sides is calculated.

Mobility of the implants or their suprastructures will be assessed manually by clinical investigation using the back part of the handles of two hand instruments (e.g., mouth mirror and probe). Mobility will be scored as either present or not. When mobility is present, the examiner will investigate and note the cause of mobility, i.e., technical complication(s) or loss of osseointegration.

Throughout the course of the study, if any of the aforementioned conditions require treatment, usual care will be provided.

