## Figures and Tables

**Table 1 tbl1:** Overview of examination time points and variables collected

*Time point (time from baseline)*	*Variables collected*
T_0_ (0)	Sleep bruxism, modified gingival index, peri-implant probing depth, marginal bone height, loss of osseointegration, modified plaque index, submucosal biofilm samples, awake bruxism, smoking status, periodontal parameters.
T_1_ (2 weeks)	Modified gingival index, peri-implant probing depth, marginal bone height, loss of osseointegration, modified plaque index, periodontal parameters.
T_3_ (6 weeks)	Sleep bruxism, modified gingival index, peri-implant probing depth, marginal bone height, loss of osseointegration, technical complications.
T_4_ (3 months)	Modified gingival index, peri-implant probing depth, marginal bone height, loss of osseointegration, technical complications, submucosal biofilm samples.
T_5_ (12 months)	Sleep bruxism, modified gingival index, peri-implant probing depth, marginal bone height, loss of osseointegration, technical complications, modified plaque index, submucosal biofilm samples, awake bruxism, smoking status, periodontal parameters.
T_6_ (24 months)	Modified gingival index, peri-implant probing depth, marginal bone height, loss of osseointegration, technical complications.

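### Hypothesis 2 concerns differences in bone, but the regression names bone height, pocket depth and bleeding themselves, with no baseline value among the listed covariates

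*Protocol article*

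**What the plan says.** Under Objective of the present study, the second null hypothesis is that "SB is not associated with the occurrence of biological complications", and its outcomes are "differences in marginal bone height, peri-implant bleeding on probing, pocket depths and loss of osseointegration".

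Under Biological complications, bone height is a per-film measurement: "Marginal bone height will be measured on each radiograph using the appropriate tool of the program as the vertical distance (mm"), taken from the implant shoulder to the bone margin and averaged over two sides. The same section provides separately for change: "The Subtraction technique of the Emago software will be used to detect differences in marginal bone between subsequent radiographs". Probing depth is a mean in millimetres per implant. For bleeding, "Peri-implant bleeding on probing will be scored per implant according to the Modified Gingival Index", which runs from 0 to 3.

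Under Single/multiple analysis, the test is: "Possible associations between SB and bleeding on probing, pocket depths and marginal bone height will be tested by means of linear regression analysis". The models are described as multilevel, and the only source of dependency named is several implants in one person.

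Covariates and confounders lists smoking, awake bruxism, plaque and periodontal parameters. The periodontal parameters leave out the implants under study. Table 1 records at baseline: "Sleep bruxism, modified gingival index, peri-implant probing depth, marginal bone height, loss of osseointegration, modified plaque index, submucosal biofilm samples". The three outcomes recur at all five later visits. Study design places baseline at the impression appointment, before the definitive prosthesis exists.

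**The concern.** The protocol has one term for the level of bone and another for its change. The objective uses the change, and the analysis section uses the term defined as a level. A distance from the implant shoulder depends partly on where the shoulder sat when the implant was placed and healed, before the prosthesis carried any load. If SB happens to be associated with that starting position, a regression of levels shows an SB association that is not deterioration under load. If it is not, the starting differences are simply noise.

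Pocket depth and bleeding raise the same issue in a weaker form. The word for differences clearly governs only bone. However, the hypothesis speaks of complications occurring, which implies something that arises during follow-up, and no starting value is named for these outcomes either.

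At stake are the meaning of an SB coefficient for three of the four hypothesis 2 outcomes, and the precision of the estimate in about 98 participants.

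**Working it through.** **The protocol's own figure.** The Sample size section uses 50 + 8k with k = 6: 50 + 48 = 98, which reproduces. The six predictors are not listed. One count reaches six without an outcome baseline: SB, smoking, awake bruxism, plaque, pockets of 5 mm or more, and Bleeding Index.

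**Sections side by side.**

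| Place | Bone quantity |
|---|---|
| Objective | differences in marginal bone height |
| Biological complications | height on each film (level); subtraction between films (change) |
| Single/multiple analysis | marginal bone height |
| Covariates and confounders | no starting value of the outcome listed |
| Table 1 | starting value collected |

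The periodontal parameters cannot stand in for the starting value, because they exclude the studied implants.

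**Precision.** Let rho be the correlation between an implant's reference value and one follow-up value. The article gives no rho, so a range is assumed, with equal variances at both times. Relative to an unadjusted follow-up level (variance 1):

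- change score: 2(1 − rho)
- level with reference value as covariate: 1 − rho²

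| rho | change | baseline-adjusted | reduction by adjustment |
|---|---|---|---|
| 0.3 | 1.40 | 0.91 | 9% |
| 0.5 | 1.00 | 0.75 | 25% |
| 0.7 | 0.60 | 0.51 | 49% |
| 0.8 | 0.40 | 0.36 | 64% |

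The adjusted level has the smallest variance throughout. A change score is worse than the plain level when rho is below 0.5.

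**Dilution, if all six visits were pooled without a time term.** This is an assumption; the article does not say it. Take an SB effect that is constant after loading and zero before it:

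- one pre-loading visit (baseline): 5/6 = 83% of the effect
- two pre-loading visits (2 weeks as well): 4/6 = 67%

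Only baseline is documented as preceding the prosthesis. The 2-week status is an inference: Table 1 first lists technical complications at 6 weeks, and no placement date is given.

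**Choosing the reference visit.** Study design numbers baseline and 2 weeks as T1 and T2; Table 1 numbers them T0 and T1. A reference named by label would therefore be ambiguous. For bone there is a further point: the silicone mould that makes the films reproducible is made only once the suprastructure is in place, so the baseline film precedes that standardisation.

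**Effect on the stated size.** One added predictor under the protocol's rule: 50 + 8 × 7 = 106, eight more than 98.

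**The case against.** The analysis sentence is a summary in a journal article. It names variables and a model family and is silent on level versus change, baseline term and visits. Such detail commonly sits in a fuller document, and the covariate list opens as a non-exhaustive one. The planned subtraction of films shows that change in bone is intended in some form, so the analysis section may use marginal bone height as shorthand for it. All of this stands, and it limits the claim to a conflict in wording that must be resolved. It does not remove the conflict, because the document uses separate terms for level and change and its analysis section uses the level term.

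Several stronger readings are tempting and are not supported:

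- *The model certainly uses raw levels and includes pre-loading visits.* No section says so. The visits are collected; their entry into the model is not stated.
- *The study cannot show that SB came before deterioration.* SB is recorded at baseline, 6 weeks and 12 months, and outcomes run to 24 months. The design allows temporal ordering.
- *The loss equals a known number of participants.* Dividing 98 by 1 − rho² gives 131 at 0.5 and 272 at 0.8, but only for one value per independent participant, not for clustered implants with repeated visits.
- *The 0 to 3 bleeding score needs an ordinal model.* In a simulation (98 participants, 60% or 80% zeros, 600 runs per setting), type I error was 4% to 7% for both models. Power was 0.76 linear against 0.80 ordinal, and 0.61 against 0.67, when SB was symmetric. With skewed SB it was 0.79 against 0.78, and 0.74 against 0.72. The gain is small and inconsistent.

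**Conclusion.** The point holds as a mismatch that should be reconciled. The stated bone outcome is a difference, the named dependent variable is a level, and the listed covariates omit a starting value that is already collected. Pocket depth and bleeding share the missing starting value, but the change-versus-level conflict in wording is explicit only for bone.

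The size cannot be fixed from the document. The 25% to 64% reduction in residual variance rests on assumed correlations of 0.5 to 0.8 and a single follow-up value. The 83% and 67% figures rest on pooling without a time term and on a constant post-loading effect, and the second also requires that the 2-week visit precedes loading. The case for change does not depend on any one of these numbers: the data are in hand, and the change aligns the test with the hypothesis.

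**What to change.** State one model for each of bone height, pocket depth and bleeding:

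- outcome: the value at post-loading visits only
- covariate: the same implant's reference value, alongside the listed covariates
- terms: SB, visit and SB-by-visit
- random effects: participant and implant
- test of hypothesis 2: the SB effect at 24 months

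Use the impression-appointment visit as a covariate and never as an outcome. Name the reference visit by time from baseline, not by T label, and say whether the 2-week visit precedes loading. For bone, choose between the baseline film and the first film taken with the mould, and give the reason. A later reference is better standardised, but it leaves any earlier change outside the comparison. Say also whether the subtraction result enters the model or serves only as a check. Then bring the objective, the measurement section and the analysis section into the same terms. Because SB is not randomised, a change score and a baseline-adjusted level can give different answers, so one should be named in advance.

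The cost is plan wording and modest programming. With four outcome visits (6 weeks, 3, 12 and 24 months), a categorical visit term adds three parameters and its interaction with SB three more, plus one for the reference value. Counting only the reference value as a predictor, the protocol's rule nominally gives 106 participants instead of 98. No new measurement is needed.

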## Discussion

To our knowledge, this is the first clinical prospective cohort study to investigate the associations between SB and dental implant treatment complications.

Certain strong points of this investigation should be recognised. First, the study aims to answer a clinically relevant question, for which the literature so far is inconclusive. A strength of our design is the clear distinction between sleep and awake bruxism that is made. Given the possibility that the different types of bruxism may be differently associated with implant failure, together with the fact that these two conditions require different management approaches,^
49
^ employs that this distinction will enhance the clinical applicability of our results. SB will be diagnosed by means of EMG recordings. Though less valid than the gold standard, i.e., PSG recordings with audio-visual recordings, this feasible diagnostic method is a good proxy, and by performing repeated measurements it enables capturing the time-variant nature of SB. What is more, by extensively documenting our study procedures and the careful data management, we aim to contribute to the performance of transparent and reproducible research.

On the other hand, certain limitations should be acknowledged. For one, no patient-related outcomes, such as satisfaction with the prosthesis, aesthetics or function, will be assessed. Also, no outcomes related to complications-associated costs of treatment will be studied. Though it would be of interest to investigate these parameters, they were not included in our protocol for the sake of avoiding a too complex study design. Future investigations should address these outcomes. Also, our patient sample is derived from a dental school, thus it could be hypothesised that it differs from the population attending other dental care facilities. However, no data are available today to describe if and how these populations might differ from each other.

## Figures and Tables

**Table 1 tbl1:** Overview of examination time points and variables collected

*Time point (time from baseline)*	*Variables collected*
T_0_ (0)	Sleep bruxism, modified gingival index, peri-implant probing depth, marginal bone height, loss of osseointegration, modified plaque index, submucosal biofilm samples, awake bruxism, smoking status, periodontal parameters.
T_1_ (2 weeks)	Modified gingival index, peri-implant probing depth, marginal bone height, loss of osseointegration, modified plaque index, periodontal parameters.
T_3_ (6 weeks)	Sleep bruxism, modified gingival index, peri-implant probing depth, marginal bone height, loss of osseointegration, technical complications.
T_4_ (3 months)	Modified gingival index, peri-implant probing depth, marginal bone height, loss of osseointegration, technical complications, submucosal biofilm samples.
T_5_ (12 months)	Sleep bruxism, modified gingival index, peri-implant probing depth, marginal bone height, loss of osseointegration, technical complications, modified plaque index, submucosal biofilm samples, awake bruxism, smoking status, periodontal parameters.
T_6_ (24 months)	Modified gingival index, peri-implant probing depth, marginal bone height, loss of osseointegration, technical complications.
